#### ***Pharmacokinetics (PK):***

Blood sampling for PK assessment will be carried out in all patients on day of clip ligation (0, 6, 12 and 24 hours post clip ligation,  $\pm 20$  minutes each), day 8, day 14 after aneurysm rupture and before discharge or day 21 (whichever occurs first). Blood sampling for PK assessment will additionally be done every time blood is drawn for medical reasons up to patient discharge or day 21 but only once per day.

Single cerebrospinal fluid (CSF) samples obtained from patients provided for medical reasons with an external ventricular drain (EVD) will be collected every time a CSF sample is removed for medical reasons and up to patient discharge or to day 21, to determine nicardipine levels.

Only samples collected in patients treated with NicaPlant® will be analysed at the end of this study.

Where possible, the following PK parameters will be determined:

- Maximum plasma concentration ( $C_{max}$ ), obtained directly from the observed concentration versus time data
- Time of maximum plasma concentration ( $t_{max}$ ), obtained directly from the observed concentration versus time data
- Area under the plasma concentration time curve from zero (pre-dose) extrapolated to infinity ( $AUC_{0-\infty}$ ), calculated by linear up/log down trapezoidal summation and extrapolated to infinity by addition of the last quantifiable concentration divided by the elimination rate constant:  $AUC_{0-t} + C_{last}/\lambda_z$ . If the extrapolated area ( $C_{last}/\lambda_z$ ) is greater than 20% of  $AUC_{0-\infty}$ , then  $AUC_{0-\infty}$  and related parameters may not be reported
- Area under the plasma concentration-time curve during the dosing interval ( $AUC_{0-t}$ ) in Part B only, calculated by linear up/log down trapezoidal summation
- Half-life ( $t_{1/2}$ , h). Visual assessment will be used to identify the terminal linear phase of the concentration-time profile. A minimum of 3 data points will be used for determination

- 326 • Apparent systemic clearance (CL/F, L/h)
- 327 • Apparent volume of distribution ( $V_z/F$ , L)
- 328 • The time interval (h) of the log-linear regression to determine  $t_{1/2}$  ( $t_{1/2}$ , Interval)
- 329 • Number of data points ( $t_{1/2}$ , N) included in the log-linear regression analysis to  
330 determine  $t_{1/2}$
- 331 • Coefficient of determination (Rsq) for calculation of  $\lambda_z$ . If Rsq is less than or equal to  
332 0.800,  $\lambda_z$  and related parameters will not be reported
- 333 • Percentage of AUC obtained by extrapolation (%AUCex)

334

### 335 ***Pharmacodynamics (PD):***

336 The pharmacodynamic endpoints are incidence of moderate to severe angiographic  
337 measurements of cerebral vasospasm and new cerebral infarcts as assessed by the  
338 independent neuroradiologist, and DIND.

339

## 340 **STUDY DESIGN**

### 341 **Overall study design and plan description**

342 This study is a randomised, single-blind, parallel-group design comparing 10 NicaPlant®  
343 implants / patient versus standard of care in overall 40 patients who have had aSAH.

344 The two groups of patients will be subjected to the following treatments:

- 345 • Standard of care plus NicaPlant®.
- 346 • Standard of care.

347 Both groups of patients will receive the standard of care according to treatment guidelines [8]  
348 and all further medical care will not be different between the groups. Patients in the  
349 interventional group will only in addition receive NicaPlant® implants.

350 NicaPlant® will be administered as per the implantation protocol, (in brief: by placement  
351 during microsurgical clipping of the ruptured aneurysm in proximity to all of the exposed  
352 cerebral blood vessels).

353 Patients will be assessed to determine the efficacy of NicaPlant® application to reduce the  
354 occurrence of angiographic cerebral vasospasm and to prevent early morbidity/mortality  
355 following aSAH. Cerebral vasospasm will be assessed by analysis of angiograms to  
356 determine narrowing of the proximal blood vessels.

357 Clinical Outcomes will be recorded at 12 weeks and 1 year (52 weeks) after the aSAH. Safety  
358 assessments will be made to confirm the safety and tolerability of the selected dose of  
359 NicaPlant®.

360 A data safety monitoring board (DSMB) will be set-up to monitor safety throughout the trial  
361 period and provide recommendations for any necessary actions. A steering committee will  
362 receive and review the blinded reports from the DSMB and take action as appropriate.

363 The DSMB will convene after 20 patients have been recruited and monitored to discharge, or  
364 day 21, whichever occurs earlier.

365 The final analysis will be carried out when the last patient completes the week 12 assessment,  
366 the database has been locked at this time point and unblinding has occurred. Data collected  
367 for patients at Week 52 after aSAH will be analysed and included as an addendum to the final  
368 report.

## 369 **Discussion of study design, including the choice of control groups**

### 370 ***Randomisation***

371 This is a randomised, single blind study. Patients will be randomised to either the standard of  
372 care plus treatment group or standard of care group. Therefore, twenty patients will receive  
373 standard of care plus 10 NicaPlant® implants, and twenty will be assigned to the standard of  
374 care control group.

### 375 ***Blinding***

376 The study design does not include a placebo implant for ethical reasons; therefore, it is not  
377 possible to blind the neurosurgeons performing the aneurysmal clipping procedure to study  
378 treatment. Accordingly, the standard of care control group will receive no intracranial  
379 treatment (i.e., no placebo implants).

380 Patient selection bias is controlled by randomisation; patients will be blinded to which  
381 treatment they are receiving (implant or standard of care group) throughout the study i.e. the  
382 study is single blinded.

383 Therefore, the treatment groups are as follows:

- 384 • Patients receiving standard of care and NicaPlant® implants.

385 OR

- 386 • Patients in standard of care.

387 Patients will be assigned a corresponding randomisation code at consent; in the operation  
388 room, following aneurysm clip ligation, a member of the unblinded operation room team will  
389 verify the randomisation code using the IWRS system; if the patient is to receive NicaPlant®  
390 implants the implantation procedure goes ahead; if not, no implantation is carried out.

391 In emergency situations, when the identity of the treatment arm must be made known, the  
392 treatment arm of the patient will be available to designated and authorised personnel using  
393 the IWRS system. Access to the IWRS is held by the responsible neurosurgeon and other

designated authorised site personnel, to be agreed prior to study commencement. Full details of the randomisation including user access will be provided in the study IWRS user guide.

Study team staff (including those undertaking Safety Assessments, TCD readings, mGCS assessments and Clinical Outcome assessments) will be blinded to the treatment. An independent specialist, also blinded to the treatment, will undertake the analysis of the angiograms and computed tomography imaging of the brain for the diagnosis of cerebral vasospasm and new cerebral infarcts, respectively, for study endpoint assessment.

Trained personnel collecting data on clinical outcome at week 12 and 52 will also be blinded. In cases of DIND or anti-vasospasm rescue therapy as determined by the sites, all required data (e.g. clinical data, case narratives, angiograms, CTs) will be provided to a board of blinded independent experts to adjudicate on the presence of DIND or anti-vasospasm rescue therapy.

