## 505 TREATMENT(S)

### 506 Appearance and content

#### 507 *Investigational Medicinal Product*

508 NicaPlant® is a nicardipine modified release formulation, it is presented in the form of a rod-  
509 shaped implant (2 mm x 10 mm, 4 mg nicardipine load).

510 NicaPlant® will be given on top of the standard of care-treatment as determined at the sites  
511 according to the treatment guidelines. [8]

512 A main difference to the previous study is the lack of limitations for an additional treatment  
513 with Nimodipine or any other treatment needed according the treatment guidelines since the  
514 safety of patient should not be reduced. Furthermore, the sovereignty of the study sites will  
515 not be subducted by the study since patients in emergency situations within the intensive care  
516 unit need an individual therapy adapted to their needs and with no delays.

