### 561 ***Blinding***

562 Blinding is described in section 0.

563 Blinding will be recorded in a blinding log – on this log, blinded and unblinded study team  
564 members will be tracked. If there is an isolated break in the blind that/those member(s) of the  
565 research team must be transferred to the unblinded team.

566 For purpose of clarity, the un-blinded and blinded personnel is listed in the following table.

| Un-blinded                                                                         | Blinded                                                                                                                                                                                                                                                                                                                                                                                                                                                    |
|------------------------------------------------------------------------------------|------------------------------------------------------------------------------------------------------------------------------------------------------------------------------------------------------------------------------------------------------------------------------------------------------------------------------------------------------------------------------------------------------------------------------------------------------------|
| 

• Implantation operation room Team

 | 

• ICU team, undertaking Safety Assessments, TCD readings and GCS assessments and angiograms and computer tomography scans for patient management decisions.

• Independent specialist undertaking analysis of the angiograms and CT/MRI brain scans for the diagnosis of vasospasm and new cerebral infarcts.

• Trained personnel collecting data on clinical outcome and mortality week 12

 |

|  |                                                                                                                                                                  |
|--|------------------------------------------------------------------------------------------------------------------------------------------------------------------|

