|  | 
and week 52.
 
 
Independent experts adjudicating on the presence of DIND and anti-vasospasm rescue therapy
 
 |
|--|------------------------------------------------------------------------------------------------------------------------------------------------------------------|

567

568

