## **Other exploratory endpoints**

- Incidence of vasospasm-related morbidity/mortality within 14 days post-aneurysm rupture, or before patient discharge, defined by at least one of the following:
  - a) DIND
  - b) Death caused by vasospasm, delayed ischemic neurological deficit (DIND), infarcts or complications due to anti-vasospasm therapy
  - c) The need for anti-vasospasm rescue therapy within patient discharge
- Daily assessment of modified Glasgow Coma Scale (mGCS) up to patient discharge or day 21.
- Clinical outcome at Weeks 12 & 52 post-aneurysm rupture as measured by:
  - Modified Rankin Scale (mRS)
  - Glasgow Outcome Scale (Extended) (GOSE)
  - Montreal Cognitive Assessment tool (MoCA)
  - Health related quality of life assessed using the EQ-5D-5L and SF36
  - Mortality due SAH

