### ***Delayed Ischemic Neurological Deficit***

Delayed Ischemic Neurological Deficit (DIND), also referred to as cerebral ischaemia, is defined according to the definition proposed by a multidisciplinary research group and reported on Stroke in 2010 [15]. Vergouwen M.D., Vermeulen M., van Gijn J., Rinkel G.J., Wijdicks E.F., Muizelaar J.P., Mendelow A.D., Juvela S., Yonas H., Terbrugge K.G., Macdonald R.L., Diringer M.N., Broderick J.P., Dreier J.P., Roos Y.B. Definition of delayed cerebral ischemia after aneurysmal subarachnoid hemorrhage as an outcome event in clinical trials and observational studies: proposal of a multidisciplinary research group. Stroke. 2010 41(10):2391-5]. DIND is the occurrence of focal neurological symptoms impairment (such as hemiparesis, aphasia, apraxia, hemianopia, or neglect), or a decrease of at least 2 points on the GCS in awake patients (either on the total score or on one of its individual components [eye, motor on either side, verbal]). This should last for at least 1 hour, it is not apparent immediately after aneurysm occlusion, and cannot be attributed to other causes by means of clinical assessment, CT or MRI scanning of the brain, and appropriate laboratory studies.

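### The blinded board reviews only DIND that a site has already called, so adjudication can strike out over-called DIND but cannot recover missed DIND

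*Protocol*

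**What the plan says.** The Blinding section under Study Design opens the referral rule with "In cases of DIND or anti-vasospasm rescue therapy as determined by the sites, all required" and continues "data (e.g. clinical data, case narratives, angiograms, CTs) will be provided to a board of" blinded independent experts, who decide whether DIND or rescue therapy was present. The table of blinded and unblinded staff, in the Blinding section under Treatment(s), repeats the role ("Independent experts adjudicating on the presence of DIND and anti-vasospasm rescue therapy") and adds no further trigger.

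On who knows the allocation, the Study Design section says it is not "possible to blind the neurosurgeons performing the aneurysmal clipping procedure to study" treatment, and that the responsible neurosurgeon and other designated site staff hold IWRS access. The table lists only the operating-room team as unblinded and places among the blinded the "ICU team, undertaking Safety Assessments, TCD readings and GCS assessments and angiograms" and CT used for patient management. A log moves anyone who becomes unblinded to the unblinded team. The protocol does not say which site staff determine DIND.

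The DIND definition requires a focal deficit, or a fall of at least 2 "points on the GCS in awake patients", lasting at least an hour and not explained by another cause. Elsewhere the protocol plans "Daily assessment of modified Glasgow Coma Scale (mGCS) up to patient discharge or" day 21.

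**The concern.** A blinded board is there to make a judgement-based endpoint uniform across sites. DIND is such an endpoint. It is a diagnosis of exclusion in WFNS grade III-IV patients, so a local view that something else explains the decline settles the case before the board sees it. The board can correct one type of error (calling DIND when it is absent) and not the other (failing to call it when it is present).

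The protocol treats its imaging endpoints differently. The DSA at day 8±1 and the Visit 4 CT are scheduled for every patient and read by an independent blinded neuroradiologist whatever the site concluded. As written, that reader can classify a new infarct as vasospasm related in a patient whom the site never referred, and nobody central then asks whether that patient had DIND. An infarct is not itself DIND, but it is a clear reason to look.

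At stake is the count for an exploratory composite, which as a binary outcome is tested by Fisher's exact test, and for DIND as a descriptive pharmacodynamic endpoint.

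**Working it through.** **The plan's own figure.** Power & Sample size gives 84% power for the primary endpoint: 20 per arm, 20% vs 70%, Fisher's exact test, two-sided 5%. Exact enumeration gives 84.6%, so the figure reproduces. This point does not touch it.

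**Model.** The protocol gives no DIND rate and no figure for how completely sites call DIND, so every rate below is an assumption. Let p_c and p_t be the true DIND risks (control, implant) and s the share of true cases that the site calls. Assume that the board confirms every true case it receives and removes every false one. Then:

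- observed risk = s × true risk
- observed risk difference = s × (p_c − p_t)
- observed risk ratio = (s × p_t)/(s × p_c) = p_t/p_c, unchanged when s is equal in both arms

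**Equal under-calling, worked case.** p_c = 50%, p_t = 25%, s = 0.7:

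- control 0.7 × 50% = 35%; implant 0.7 × 25% = 17.5%
- difference 17.5 points instead of 25; ratio 0.5 before and after
- with 20 per arm, 10 + 5 = 15 expected true cases become 7 + 3.5 = 10.5, so 4.5 are lost

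**Equal under-calling, range** (20 per arm, two-sided Fisher, 5%):

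| True risks, control/implant | s = 1: difference, power | s = 0.8 | s = 0.6 |
|---|---|---|---|
| 30% / 10% | 20 points, 24% | 16 points, 17% | 12 points, 10% |
| 40% / 15% | 25 points, 32% | 20 points, 23% | 15 points, 15% |
| 50% / 20% | 30 points, 41% | 24 points, 29% | 18 points, 19% |

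Power is low even with complete ascertainment, so this endpoint would not be decisive in either case.

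**From DIND to the composite.** These figures are for DIND alone. Under Exploratory Outcome Endpoints the composite is also met by related death or need for rescue therapy, so a missed DIND that was treated with rescue therapy still counts and the loss is smaller. The statistical section lists need for rescue therapy as a separate item; if it is analysed that way, this protection does not apply to the item made up of DIND and related death.

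**What bias between arms would need.**

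- *Unequal calling by arm.* With no true effect, a 40% risk in both arms, and 80% of control but 60% of implant cases called: 0.8 × 40% = 32% vs 0.6 × 40% = 24%, a false difference of 8 points. This requires the allocation to be known to whoever makes the call.
- *Unequal calling by site.* Two sites calling 95% and 60% of cases, true risk 40% in both arms. With half of each arm at each site, both arms show 40% × (0.5 × 0.60 + 0.5 × 0.95) = 31%, no bias. With 60% of implant and 40% of control patients at the low-calling site: implant 40% × (0.6 × 0.60 + 0.4 × 0.95) = 29.6%, control 40% × (0.4 × 0.60 + 0.6 × 0.95) = 32.4%, a false difference of 2.8 points. At 70% and 30% it is 33.8% − 28.2% = 5.6 points.

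**The case against.** Several points on the other side stand.

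- *Low stake.* The composite is exploratory and the pharmacodynamic endpoints are summarised descriptively. The primary and secondary endpoints do not depend on the site's call.
- *Rescue therapy is hard to miss.* It is defined as a short list of interventions that leave a treatment record. The point is really about DIND.
- *Over-calls are dealt with.* A reader might infer that all differences between sites in calling events stay in the result. The board removes over-calls, so only under-calling remains, and it does not bias the comparison when the arms are balanced within site.
- *The screen is imperfect.* The GCS criterion covers awake patients with a deficit of at least an hour. A once-daily mGCS can miss a short deficit, and the visit schedule lists no daily focal-deficit examination.

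Two stronger readings are tempting. A reader might infer that unblinded surgeons suppress DIND calls in the implant arm and so create a false benefit. The documents do not support this: no section gives the operating surgeon the DIND call, the ICU team and study assessors are listed as blinded, a log handles breaks in the blind, and access to the treatment arm through the IWRS is described for emergencies. What remains is that the person making the call is not named, so leakage is possible but not shown. A reader might also take the sentence beginning "Furthermore, the sovereignty of the study sites will" as leaving endpoint calling to each site. It concerns individual therapy in emergencies and says nothing about endpoint determination.

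It can also be said that nothing bars the board from asking for more cases, and that working rules for the board, not shown here, might widen its remit. That is possible, but the protocol itself states a referral rule, and that rule is one-way.

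**Conclusion.** The point holds in a limited form. As the protocol stands, confirmed DIND can only equal or fall below site-called DIND. The expected consequence is lost events and a smaller risk difference in an exploratory endpoint: a shrinkage in proportion to the share of cases not called, with the risk ratio unchanged if under-calling is equal in the two arms. In the worked case this is 25 points reduced to 17.5 for DIND alone, and less for the composite where the missed case also had rescue therapy. Bias between arms would need leaked allocation, or site differences in calling combined with arm imbalance within sites; neither is shown. All DIND rates and calling rates here are assumptions. The change is worth making because it is cheap, not because the trial's main conclusions depend on it.

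**What to change.** Amend the referral rule in the Blinding section under Study Design so that, besides site-called cases, the existing blinded board receives every patient with any of:

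1. a recorded fall of at least 2 points in the daily mGCS after clipping;
2. a new infarct on the centrally read Visit 4 CT;
3. any recorded intervention from the protocol's list of anti-vasospasm rescue therapies.

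Sending all 40 patients would be simpler still. State that operative notes revealing implantation are withheld from the packages, and name the site role that determines DIND.

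The cost is revised wording, a database flag and some more cases for the board; patient care does not change. The screen reduces dependence on the site's call but does not remove it, because daily scores can miss short deficits and focal deficits still rest on site notes.

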### 275 **Exploratory Outcome Endpoints**

276 The exploratory outcome endpoints are:

- 277 • Incidence of vasospasm-related morbidity/mortality within 21 days or before  
278 patient discharge, defined by at least one of the following:
  - 279 a. DIND.
  - 280 b. Death caused by vasospasm, delayed ischemic neurological deficit (DIND),  
281 infarcts or complications due to anti-vasospasm therapy.
  - 282 c. The need for anti-vasospasm rescue therapy.
- 283 • Length of Intensive Care Unit (ICU) stay
- 284 • Length of Hospital Stay
- 285 • Clinical outcome at Week 12 post-aneurysm rupture as measured by:
  - 286 a. Modified Rankin Scale (mRS) – “Good Outcome” defined as mRS of 0 to 2
  - 287 b. Glasgow Outcome Scale (Extended) (GOSE) – “favourable outcome” of 6-8,  
288 “unfavourable outcome” of 0-5
  - 289 c. Montreal Cognitive Assessment tool (MoCA) - score 0-30 higher better
  - 290 d. Health related quality of life assessed using the EQ-5D-5L and SF36.

- Long-term Clinical outcome at Week 52 post-aneurysm rupture as measured by:
  - a. Modified Rankin Scale (mRS) – “Good Outcome” defined as mRS of 0 to 2
  - b. Glasgow Outcome Scale (Extended) (GOSE) – “favourable outcome” of 6-8, “unfavourable outcome” of 0-5
  - c. Montreal Cognitive Assessment tool (MoCA) - score 0-30 higher better
  - d. Health related quality of life assessed using the EQ-5D-5L and SF36.

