633 **suspected by sonographic or clinical means).**

634       • Angiographic assessment for vasospasm (even if no clinical evidence is present); if  
635       the patient develops clinical or sonographic changes suggestive of vasospasm prior to  
636       day 8, an angiogram will be performed to confirm the vasospasm and the  
637       angiographic measurement will replace the one scheduled at day 8±1 (Visit3). Both  
638       ICA and the dominant vertebral artery should be documented.

639  
640       • PK Plasma sampling (time of sampling to be recorded).

641       • vital signs (BP, pulse rate, respiratory rate, temperature), ECG, haematology, serum  
642       biochemistry

643  
644 **Visit 4: before patient discharge or day 14±1 post aneurysm rupture, whichever occurs**  
645 **first**

646       • CT brain scan, for assessment of new cerebral infarcts.

647       • PK Plasma sampling (time of sampling to be recorded).)

648       • vital signs (BP, pulse rate, respiratory rate, temperature), ECG, haematology, serum  
649       biochemistry

650  
651 **Visit 5: day of patient discharge or day 21±1 post aneurysm, whichever occurs first**

652       • PK Plasma sampling (time of sampling to be recorded).).

653       • vital signs (BP, pulse rate, respiratory rate, temperature), ECG, haematology, serum  
654       biochemistry

655       • Modified Rankin Scale (mRS)

656  
657 **Visit 6: Week 12 post aneurysm rupture**

658       • Modified Rankin Scale (mRS)

659       • extended Glasgow Outcome Scale (GOSE)

660       • Montreal Cognitive Assessment tool (MoCA)

- 661 • Health related quality of life assessed using the EQ-5D-5L and SF36
- 662 • Mortality due to SAH

663

664 **Visit 7: Week 52 post aneurysm rupture (Data to be reported in a CSR addendum)**

- 665 • Modified Rankin Scale (mRS)
- 666 • extended Glasgow Outcome Scale (GOSE)
- 667 • Montreal Cognitive Assessment tool (MoCA)
- 668 • Health related quality of life assessed using the EQ-5D-5L and SF36
- 669 • Mortality due to SAH

670

671

672 **STUDY PROCEDURES / EVALUATIONS**

673 **Safety Measurements**

674 The following safety parameters will be recorded according to the trial protocol:

- 675 • Adverse events (AEs)
- 676 • Shunt-dependent hydrocephalus
- 677 • Bacterial meningitis
- 678 • Change in grading of AE severity
- 679 • Vital Signs: blood pressure, pulse rate, respiratory rate and body temperature
- 680 • Electrocardiogram (ECG)

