- 681 • Full blood count, urea and electrolytes, liver function tests, C-reactive protein

682 **Efficacy Measurements**

683 The following efficacy parameters will be recorded according to the trial protocol:

- 684 • Incidence of moderate to severe cerebral angiographic vasospasm assessed by digital subtraction angiography (DSA) within at  $8 \pm 1$  days after aneurysm rupture where angiographic vasospasm is defined as a  $\geq 33\%$  reduction in diameter in at least one vessel segment by comparison to preoperative (pre NicaPlant® implantation) angiography and/or qualitatively assessed as moderate to severe vasospasm (in case the baseline measurement is missing). A day  $8 \pm 1$  angiogram will be performed even if the patient has no clinical or sonographic evidence of vasospasm.

691 If the patient develops clinical or sonographic changes suggestive of vasospasm prior  
 692 to day 8, and angiogram (DSA) will be performed to confirm the vasospasm and the  
 693 angiographic measurement will replace the one scheduled at day  $8 \pm 1$ . In case the  
 694 patient develops clinical or sonographic changes suggestive of vasospasm after the

day 8±1 and prior to patient discharge or day 21, an angiogram (DSA) will be performed to confirm the vasospasm, unless this is not clinically indicated.

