### ***PD:***

The pharmacodynamic endpoints are incidence of moderate to severe angiographic measurements of cerebral vasospasm and new cerebral infarcts as assessed by the independent neuroradiologist and DIND.

734 **Definitions of Assessments**

735 *World Federation of Neurological Surgeons Grading System for Subarachnoid*  
736 *Haemorrhage (WFNS)*

737 The WFNS is a 5-point scale that is a simple, reliable and clinically valid way to grade a  
738 patient with aSAH. This system offers less inter-observer variability than some of the earlier  
739 classification systems.

740 The grading is based on the Glasgow coma score (GSC see later description).

741 Grade 1            GCS score of 15 without focal deficit

742 Grade 2            GCS score of 13 or 14 without focal deficit

743 Grade 3            GCS score of 13 or 14 with focal deficit

744 Grade 4            GCS score of 7-12

745 Grade 5            GCS score of 3-6

746 *Assessment of Cerebral Vasospasm and New Cerebral Infarct by a Centralised*  
747 *Neuroradiologist Efficacy Assessment.*

748 All angiograms and computed tomography of the brain are to be evaluated locally for patient  
749 management decisions based on the local standard procedures.

750 For the assessment of the efficacy of NicaPlant® for the endpoint analysis, angiograms and  
751 computed tomography scans of the brain are to be analysed by an independent blinded  
752 neuroradiologist.

753 For this purpose, diameters of the proximal vessel segments (C1, M1, A1, P1, BA see  
754 diagram below) are to be measured in the baseline and the follow-up angiograms. To  
755 overcome potential bias from angiograms with different magnifications, the following  
756 procedure will be used:

- 757            1. The angiograms are to be optically magnified 5× to measure different vascular  
758            sections more precisely.
- 759            2. Measurements are performed on an arterial filling image in the lateral view for C1 and  
760            C5 and AP view for the other vessel segments.
- 761            3. Diameters (i.e. the contrast agent filled compartment of the vessel) are to be measured  
762            digitally in absolute values.
- 763            4. A ratio is to be built between all intradural and one extradural proportion (C5) of the  
764            vessel tree (as established by Weir and co-workers).

---

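### DIND, rescue therapy and their composite can partly follow the primary-endpoint angiogram, because the DIND board is sent the angiograms and rescue counts as an event whatever prompted it

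*Protocol*

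**What the plan says.** **Adjudication.** The Blinding section under Discussion of study design starts the process at the site: "In cases of DIND or anti-vasospasm rescue therapy as determined by the sites". It then says that all required "data (e.g. clinical data, case narratives, angiograms, CTs) will be provided to a board of" blinded independent experts, who rule on the presence of DIND or rescue. Nothing in the protocol withholds the angiograms while DIND is judged or sets an order for the two rulings.

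**DIND definition.** The Delayed Ischemic Neurological Deficit section asks for a focal deficit or a GCS fall of at least 2 points lasting at least an hour, which "cannot be attributed to other causes by means of clinical assessment, CT or MRI scanning of the brain, and appropriate laboratory studies". Angiography is not among the listed means.

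**Angiography.** Visit 3 of the Study Plan (day 8±1) lists "Angiographic assessment for vasospasm (even if no clinical evidence is present); if", and Efficacy Measurements repeats that the "angiogram will be performed even if the patient has no clinical or sonographic evidence of vasospasm". The section on centralised neuroradiology assessment adds: "All angiograms and computed tomography of the brain are to be evaluated locally for patient" management decisions.

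**Rescue.** The Anti-vasospasm rescue therapy section defines rescue by the procedures given and refers to guidelines. It states no clinical trigger of its own. Exploratory Outcome Endpoints lists "The need for anti-vasospasm rescue therapy" as one of three items, any one of which makes a vasospasm-related morbidity/mortality event. Exploratory objectives and Other exploratory endpoints do the same. The Efficacy Endpoints part of the statistics section differs: its morbidity/mortality endpoint covers DIND and the specified deaths, and rescue is a separate endpoint.

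**The concern.** Blinding to arm normally protects adjudication because the board has nothing to tie a patient to a treatment. Here the board holds the primary-endpoint image, which is the variable the drug is meant to change. Excluding other causes of a deterioration is a judgement. A deterioration with open vessels is easier to ascribe to something else, and there will be more open vessels on NicaPlant if the drug works on the angiogram.

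Rescue has a more direct link. A scheduled DSA in a patient without symptoms is read locally for management and may lead to rescue. That rescue is then an event, and no section asks whether a clinical change or the image prompted it.

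At stake is what these endpoints can show. The overall design section aims at preventing early morbidity/mortality as well as vasospasm. The Population section cites a trial of another compound in which vasospasm fell but good outcome in grade I and II patients did not improve (46% vs 55% on control). Image and clinical benefit can therefore part company on the protocol's own account, and endpoints that partly restate the image cannot show whether they have.

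**Working it through.** **The plan's own figure.** Power & Sample size gives 20 per arm, vasospasm 20% active vs 70% control, Fisher's exact test, two-sided 5%, power 84%. Exact enumeration of all 21 × 21 outcomes, rejecting at p ≤ 0.05, gives 0.846. The figure reproduces and is not in dispute. The 20% and 70% are carried forward as p.

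**Inputs the protocol does not give (assumptions).** True deterioration d = 40% in both arms, independent of vasospasm, so there is no true treatment effect. The board confirms a fraction s of called cases with vasospasm and u of those without. A fraction r of non-deteriorating patients with vasospasm on DSA receive rescue.

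**Step 1, DIND.** Adjudicated rate = d × [p·s + (1 − p)·u].

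| s / u | Control (p = 0.7) | NicaPlant (p = 0.2) | Ratio |
|---|---|---|---|
| 95% / 70% | 0.4 × (0.665 + 0.21) = 0.350 | 0.4 × (0.19 + 0.56) = 0.300 | 0.86 |
| 90% / 50% | 0.4 × (0.63 + 0.15) = 0.312 | 0.4 × (0.18 + 0.40) = 0.232 | 0.74 |
| 90% / 30% | 0.4 × (0.63 + 0.09) = 0.288 | 0.4 × (0.18 + 0.24) = 0.168 | 0.58 |

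With s = u the difference is zero, so the whole effect comes from the board weighing the image. In the middle row the expected counts are 20 × 0.312 = 6.2 and 20 × 0.232 = 4.6 patients.

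**Step 2, rescue prompted by the image alone.** Added events = (1 − d) × p × r = 0.6 × p × r.

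- r = 0.25: 10.5% vs 3.0%, difference 7.5 points.
- r = 0.50: 21% vs 6%, difference 15 points.
- r = 0.75: 31.5% vs 9.0%, difference 22.5 points.

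**Step 3, DIND-or-rescue composite, leaving step 1 aside.** At r = 0.5 the rates are 40% + 21% = 61% on control and 40% + 6% = 46% on NicaPlant.

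**Step 4, how often this reaches significance.** By the same enumeration, Fisher's test favours NicaPlant at p ≤ 0.05 in 2.8%, 4.5% and 8.3% of trials for the three DIND rows, and in 8.5% for the composite in step 3. With 40% in both arms it does so in 1.2%. The main effect is a shifted estimate, less often a false significant result.

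**Step 5, the passages on rescue side by side.** Exploratory objectives, Exploratory Outcome Endpoints and Other exploratory endpoints put rescue inside the composite. The statistics section puts it outside. Their windows also differ: 21 days or discharge in the first two, 14 days or discharge in the third, discharge in the statistics section. Under either placement of rescue, the rescue endpoint itself can follow the image.

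**The case against.** The strongest defence is that the board has two tasks and the angiograms may be there for the rescue task. The DIND definition fixes how other causes are excluded, and the protocol nowhere says the angiogram decides DIND. Because a site must call the case first, the image can only tilt confirmation or rejection; it cannot create a DIND event at the board. This stands as a limit. It does not remove the problem, because one file goes to one board with no order of viewing stated.

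The magnitudes rest on assumed rates, and the rescue model attributes every imaging-only rescue to the mandated DSA. TCD is done daily, and sonographic suspicion before day 8 triggers a DSA that replaces the scheduled one, so some of these patients would be imaged anyway. This also stands.

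Four stronger readings are tempting and are not supported:

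- **All exploratory clinical outcomes are affected.** mRS, GOSE, MoCA and quality of life at weeks 12 and 52 do not go to this board, and their assessors are blinded.
- **DIND and rescue are the only in-hospital clinical evidence.** New infarct on CT is the secondary endpoint with its own blinded reader, and mGCS is recorded daily.
- **The statistics section also counts rescue as morbidity.** It lists rescue separately.
- **Imaging-only rescue should be dropped from the composite.** Early rescue may prevent DIND. Those patients would then be scored event-free, and more of them would probably be controls if the drug lowers vasospasm. That exchanges one bias for another.

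**Conclusion.** The point holds for DIND, rescue and their composite. The DIND board sees an image that its own definition does not call for and that is expected to differ by arm. Rescue counts as an event without regard to what prompted it. The sections disagree on whether rescue belongs to the composite.

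The direction favours NicaPlant if the drug reduces angiographic vasospasm and either the board or the treating team gives weight to the image. The size is not known from the protocol. Under the stated assumptions, adjudicated DIND is 31% vs 23% with no true effect (ratio 0.74, range 0.58 to 0.86), and imaging-only rescue adds 7.5 to 22.5 points of difference. A reader might infer that bias has been shown or that a false positive is likely; neither follows. The endpoints are exploratory and the primary test is untouched. The weakness is in using them as clinical support for an angiographic result, and it is cheap to reduce.

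**What to change.** 1. In the Blinding section, have the board record its DIND verdict from clinical data, narratives, CT/MRI and laboratory results, and release the angiograms for the rescue item only after that.
2. For each rescue, record whether it followed clinical deterioration, followed imaging alone, or cannot be determined. The third option is needed because most entrants are expected to be incapacitated. Record this prospectively.
3. Reconcile Exploratory objectives, Exploratory Outcome Endpoints and Other exploratory endpoints with the statistics section on whether rescue is in the composite, and align the time windows.
4. Report DIND, death and rescue (by trigger) separately beside any composite. If rescue is in the composite, keep imaging-only rescue in it.

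**Cost.** A two-step adjudication form, one added field and some wording. The DIND verdict is reached with one source fewer. Any influence of the image on the site's own DIND call remains. These changes concern scoring and reporting only; clinical care is unchanged.
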